### Blinding

The double-blind status of the trial will be maintained by ensuring rituximab and placebo infusion bags are identical in appearance at the time of dispensing from Pharmacy. Treatment allocation will only be known to the trial pharmacy and the central safety team at the CTRU. The Investigators and other members of the site staff involved with the trial will remain blinded to the allocation. All patients will receive the same pre- and post-infusion medication, and the infusion will be administered in the same way for both groups.

Emergency unblinding is permitted where knowledge of treatment allocation is necessary for the appropriate medical management of the patient. This will be performed by the safety team at the CTRU (during office hours) or the local Pharmacy team (during out of office hours). Causality and expectedness of Adverse Events/Serious Adverse Events will be assessed as though the patient received rituximab.

### Treatment schedule

Patients will receive two courses of rituximab or placebo. Each course consists of two doses of rituximab or placebo by intravenous infusion, administered at a two-week interval. The first course is at week 0 and week 2; the second course is at week 24 and week 26. See Figure 2 for details of the treatment schedule.

**Figure 2 F2:**
[figure not shown]
Treatment schedule.

### Assessments, samples and data collection

All protocol-required assessments will be entered onto paper case report forms at each site. All timings relate to first dosing at Week 0 (Day 1). An assessment of response is made at week 16, week 24, week 36 and week 48 (end of study).

The trial visits are structured as detailed in Figure 3.

• Screening visit: All patients will undergo screening within 28 days prior to the start of treatment.

• Baseline visit: Baseline assessments are to be performed after eligibility has been confirmed and within 14 days prior to the start of treatment.

• Treatment visits: All treatment visits will take place at weeks 0, 2, 24 and 26.

• Assessment visits: Patients will be assessed at weeks 16, 24, 36 and 48 for safety and outcome measures and 7 days prior to dosing at weeks 24 for safety.

• Biological samples collected from participants will be sent to the Central Laboratory at the William Harvey Research Institute, London for processing, appropriate analysis and storage. These samples will be used for a range of studies of direct relevance to the treatment of PSS.

**Figure 3 F3:**
[figure not shown]
Schedule of events.

### Sample size

A total of 110 patients will be required for this study. A sample size of 50 evaluable patients per treatment group will provide 80% power to detect a difference in response rates of 30% corresponding to 25% on placebo and 55% on rituximab, assuming a 2-sided 5% significance level. 50 patients per group will also provide at least 80% power to detect a between group difference of 30% if the placebo group event rate is as high as 50% (50% placebo and 80% rituximab). In order to allow for a 10% attrition rate, 110 patients will be randomised.

### Outcomes

The primary outcome is achievement of a 30% reduction at 48 weeks from baseline in either oral dryness or fatigue measured using visual analogue scales (VAS - Range 0-100 mm).

Secondary outcomes at weeks 16, 24, 36 and 48 are: the values of the fatigue and oral dryness scales (VAS), ocular dryness (VAS), patient global assessment of health (VAS), physician global assessments of disease activity and disease damage (0–10 Likert scales), stimulated and unstimulated salivary flow rates, lacrimal flow (Schirmers I test of ocular function), and the EULAR Sjögren’s Syndrome Patient Reported Index (ESSPRI). In addition, further quality of life, and disease damage and disease activity indices at weeks 24 and 48 will be: Medical Outcomes Survey Short Form (SF-36), EQ-5D, EULAR Sjögren’s Syndrome Disease Activity Index (ESSDAI), and the Profile of Fatigue and Discomfort – Sicca Symptoms Inventory (PROFAD-SSI). Outcomes relating to systemic disease activity features at weeks 24 and 48 are: Sjögren’s Syndrome Clinical Activity Index (SCAI), Sjögren’s Syndrome Disease Activity Index (SSDAI), Sjögren’s Syndrome Disease Damage Index (SSDDI), and Sjögren’s Syndrome Damage Index (SSDI). Further outcomes correspond to serological and peripheral blood biomarkers (haematology, biochemistry, serology and immunology assays) measured at each visit. Both patients and physicians complete an exit poll at week 48 asking them if they have suspicions as to which treatment the patient received. Outcomes relating to the optional sub-studies (Glandular histology and composition assessed by biopsy and ultrasound respectively) will be measured at weeks 16 and 48, and the T-Cell sub-study outcomes (peripheral and lesional T cells) will be assessed at week 16 for analysis in this study with samples taken at weeks 24, 36 and 48 for use in future studies.

### Statistical analysis

All analyses will be conducted on the intention-to-treat (ITT) population and patients will be analysed according to the treatment group to which they were randomised. All formal analyses will be carried out at a 2-sided 5% level of significance.

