### Randomisation

Following confirmation of eligibility, patients will be randomised on a 1:1 basis to receive either rituximab or placebo infusion, in addition to standard therapy. Randomisation will be performed using minimisation incorporating a random element, to ensure treatment groups are well-balanced for: Centre; Age (≥65 or <65); Disease Duration (≥10years or <10years); Consent for minor labial gland biopsy; Consent for ultrasound scan. Both registration and randomisation will be performed centrally using an automated 24-hour telephone system based at the Leeds Clinical Trials Research Unit.

Participating research sites will be required to complete a log of all patients over the age of 18 with PSS who are not registered for screening nor randomised either because they are ineligible or because they decline participation.

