#### Secondary outcome analyses

• Fatigue, oral and ocular dryness, patient and physician global assessments: For each symptom, a multi-level repeated measures linear regression model will be used to compare VAS scores between groups, models will include the minimisation factors (age, centre, disease duration).

• Salivary and Lacrimal Flow: The flow rates (stimulated salivary flow, unstimulated salivary flow, lacrimal flow) will be compared between the treatment groups using a multi-level repeated measures linear regression model, models will include the values at baseline and the minimisation factors.

• Quality of Life and Disease Activity Indices: The change in each Quality of Life Score, from baseline to 24 and 48 weeks, as measured by SF-36 and each Disease Activity Index (ESSDAI, ESSPRI, SF-36 and PROFAD-SSI) will be compared between treatment groups using a linear regression model, including baseline score values and the minimisation factors.

• Safety and toxicity: Safety analyses will summarise the adverse events (including serious adverse events (SAEs), serious suspected adverse reactions and suspected unexpected serious adverse events), laboratory changes and treatment-related mortality rates. Safety data will be presented by treatment group and relationship to study treatment or underlying PSS. Expected SAEs related to rituximab include infusion-related reactions, infections, cardiovascular events, hepatitis B reactivation and Progressive Multifocal Leukoencephalopathy.

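### The blanket intention-to-treat rule also covers safety, so never-infused patients enter the adverse-event denominators and events are counted under the arm assigned, not the product received

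*Protocol article*

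**What the plan says.** The Statistical analysis section opens with one population rule: "All analyses will be conducted on the intention-to-treat (ITT) population and patients will be analysed according to the treatment group" assigned at randomisation. Nothing there limits it to efficacy.

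Safety is a bullet under Secondary outcome analyses: "Safety analyses will summarise the adverse events", together with laboratory changes and treatment-related mortality. On grouping, that bullet says only: "Safety data will be presented by treatment group and relationship to study treatment or underlying PSS". The article names no safety population, no minimum exposure and no grouping by product received.

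Three other places bear on who could be affected:

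- Randomisation: "Following confirmation of eligibility, patients will be randomised on a 1:1 basis to receive either rituximab or placebo infusion". The step is tied to eligibility, not to the first infusion.
- Assessments, samples and data collection: "Baseline assessments are to be performed after eligibility has been confirmed and within 14 days prior to the start of treatment".
- Treatment schedule: "The first course is at week 0 and week 2; the second course is at week 24 and week 26", so there are four infusions per patient.

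**The concern.** Analysing by allocation protects an efficacy claim because departures from allocated treatment tend to pull the arms together. For harms, the same pull can understate risk. The safety bullet lists what is expected: "Expected SAEs related to rituximab include infusion-related reactions, infections, cardiovascular events, hepatitis B reactivation and Progressive Multifocal Leukoencephalopathy". An infusion-related reaction cannot occur in someone who was never infused. Such a patient adds to the denominator and can add nothing to the numerator. A patient who received the other product carries that product's risk into the wrong column.

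This is a rule the article states, not a detail left to a fuller document. If the full protocol or the analysis plan defines a safety set, the article's sentence contradicts it. The harm rates will also be used beyond this trial: the Background and Discussion foresee a meta-analysis with the French trial, and the Discussion foresees possible routine use.

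**Working it through.** **Inputs from the article.** The Sample size section gives 110 randomised, and allocation is 1:1, so 110/2 = 55 per arm. It plans for 50 evaluable per group, so the attrition allowance is 55 − 50 = 5 per arm.

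**The article's own figure.** For 25% v 55% at two-sided 5% and 80% power, the standard formula gives 41 per arm, or 48 with continuity correction, against the stated 50. At 50 per arm, power is 0.876 by normal approximation and 0.835 by Fisher's exact test. For 50% v 80% these are 0.894 and 0.853. Allowing for 10% attrition, 100/0.9 = 111.1, or 112 as two equal arms, against 110. The sample size is reproduced closely, and this point does not dispute it.

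**Assumptions, none from the article.** The risk of an infusion reaction among patients actually treated is 30% on rituximab and 10% on placebo. In each arm, k patients are never infused (reaction risk zero) and x receive the other product.

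**Formula under the rule as written.** Arm rate = [(55 − k − x) × own-product risk + x × other-product risk] / 55.

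For k = 3 and x = 0 in both arms:

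- rituximab: 52 × 0.30 / 55 = 15.6/55 = 28.4%
- placebo: 52 × 0.10 / 55 = 5.2/55 = 9.5%
- difference: 18.9 points; ratio: 3.0

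| Scenario | Rituximab | Placebo | Difference (points) | Ratio |
|---|---|---|---|---|
| All infused as allocated | 30.0% | 10.0% | 20.0 | 3.00 |
| 1 undosed per arm | 29.5% | 9.8% | 19.6 | 3.00 |
| 3 undosed per arm | 28.4% | 9.5% | 18.9 | 3.00 |
| 5 undosed per arm | 27.3% | 9.1% | 18.2 | 3.00 |
| 3 undosed, rituximab arm only | 28.4% | 10.0% | 18.4 | 2.84 |
| 3 undosed, placebo arm only | 30.0% | 9.5% | 20.5 | 3.17 |
| 1 per arm given the other product | 29.6% | 10.4% | 19.3 | 2.86 |
| 3 undosed and 2 given the other product, per arm | 27.6% | 10.2% | 17.5 | 2.71 |
| 5 undosed and 2 given the other product, per arm | 26.5% | 9.8% | 16.7 | 2.70 |

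Differences and ratios use unrounded rates. A set of infused patients grouped by product received gives the first row in every scenario. Five undosed per arm would use up the whole attrition allowance, so it is a generous illustration.

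**Wrong product, in counts.** Suppose 16 reactions among the 55 randomised to rituximab, 5 among 54 placebo patients treated as allocated, and one placebo-randomised patient who is given rituximab and reacts.

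- By product received: 17/56 = 30.4% v 5/54 = 9.3%.
- By randomised arm: 16/55 = 29.1% v 6/55 = 10.9%.

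The placebo rate rises by about 1.6 points and the rituximab rate falls by about 1.3. Both denominators change between the two sets, so neither shift is simply 1/55 = 1.8 points.

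**Scale against chance.** At 30% v 10% with 55 per arm, the standard error of the difference is √[(0.30 × 0.70 + 0.10 × 0.90)/55] = √(0.30/55) = 7.4 points. Three undosed per arm move the difference by 20.0 − 18.9 = 1.1 points.

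**The case against.** The strongest reply is that a journal article condenses a longer protocol. Safety sets are usually defined in that protocol or in the analysis plan, and the opening sentence may be shorthand for the comparative analyses. The safety bullet does not repeat that grouping is by randomisation, gives no denominator and specifies no test. This lowers the certainty that undosed patients will in fact be counted. It does not remove the point, because the sentence covers all analyses and safety is one of those listed.

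It is also fair that tabulating harms by randomised arm keeps the randomised comparison and is a legitimate display. That supports keeping such a table as a supplement, but not making it the only one.

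There are partial safeguards. Events are shown by relationship to treatment, and the Blinding section has causality and expectedness judged as though rituximab had been given. Individual reactions would therefore still be reported. Neither step changes a denominator or the arm in which an event is counted.

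A reader might infer more than the article supports in two ways:

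- **That the rule always shrinks the harm difference.** It does not: non-dosing in the placebo arm alone widens it, and equal non-dosing leaves the ratio for infusion reactions unchanged.
- **That the 14-day window proves a gap between randomisation and dosing.** That window governs baseline assessments. The article does not say how long before infusion randomisation takes place. A patient randomised and never infused is possible, but no frequency can be derived.

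**Conclusion.** The point stands as a fault in a stated rule, with a probably small effect. As worded, safety is summarised for everyone randomised, by assigned arm.

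Under the assumed risks of 30% and 10%, the scenarios with departures in both arms lower the difference from 20.0 points to between 19.6 and 16.7. The one-sided scenarios show that the direction depends on where the non-dosing falls. Receipt of the other product pulls the arms together whenever the two products differ in risk.

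These figures rest on assumed risks and on assumed counts of undosed and wrongly treated patients, which the article does not give. If every patient is infused as allocated, the two approaches agree exactly. The safety summaries are descriptive and the primary efficacy analysis is unaffected, so the article does not support a conclusion that harm will be materially understated.

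**What to change.** In the Statistical analysis section, limit the intention-to-treat sentence to efficacy analyses. In the safety bullet, add that safety is summarised in all patients who received any part of a study infusion, grouped by the product actually received, with anyone who received any rituximab counted under rituximab. If the full protocol or analysis plan already says this, align the article's sentence with it.

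The cost is a sentence or two and no new data, assuming that the product given at each infusion is recorded. The small downside is that the safety comparison is no longer strictly by randomised group. A supplementary table by randomised arm, stating how many patients in each arm were never infused or received the other product, covers that and shows whether the choice mattered.

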#### Primary outcome analyses

A binary logistic regression approach will model the odds of achieving a 30% reduction in symptoms for patients receiving rituximab compared to placebo. Models will include baseline scores for oral dryness and fatigue, as well as disease duration (≤10 years/>10 years), age and centre. The estimated odds ratio for treatment effect will be presented, with the associated 95% confidence interval, and p-value from a likelihood ratio test comparing the models with and without the treatment variable. In addition, the number and proportion of patients in both the rituximab and placebo groups who achieve a reduction in either oral dryness or fatigue >30% between the end of study visit (week 48) and the baseline visit will be summarised. Multiple imputation will be used to impute missing primary endpoint data.

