### Recruitment

Participant recruitment is planned over a 36-month period from a maximum of 25 centres across the United Kingdom. Patients will be approached by a research clinician during standard clinic visits. Alternatively patients may be identified by case note review and the UKPSSR and sent a Patient Invitation Letter inviting them to take part. Patients will be provided with verbal and written details about the trial (detailed Patient Information Sheet). Patients will be given at least 24 hours to read the information to consider participation. Patients will be invited to provide written informed consent before being formally assessed for eligibility by the Principal Investigator or any other qualified member of the trial team. Eligible patients from centres that have access to ultrasound and also have the facilities to perform gland biopsies will be invited to take part in the optional sub-studies to obtain minor labial gland biopsies and labial salivary gland ultrasound scans.

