### Trial status

The first patient was enrolled into TRACTISS on the 25th August 2011 and recruitment is due to end December 2013. The study is being conducted in 25 sites across the UK. We expect to report the main trial results in Autumn 2015. Ethical and governance approval for this trial has been obtained from the Leeds West Ethics Committee (ref 10/H1307/99) and the Leeds Teaching Hospitals NHS Trust respectively. The trial progress is monitored by an independent Data Monitoring and Ethics Committee (DMEC) and Trial Steering Committee (TSC).

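### Centre as an ordinary covariate in the primary logistic model, with up to 25 centres and 110 patients, read plainly puts the type I error above 5% and overstates a true odds ratio

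*Protocol article*

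**What the plan says.** Primary outcome analyses (protocol article) describes a binary logistic regression for the odds of response at week 48. Its covariates are given in one list: "Models will include baseline scores for oral dryness and fatigue, as well as disease duration (≤10 years/>10 years), age and centre". Treatment is judged by the "p-value from a likelihood ratio test comparing the models with and without the treatment variable". Statistical analysis sets a 2-sided 5% level for all formal analyses. Nothing is said there about a random effect, conditioning, pooling of small centres or penalisation.

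On numbers, Sample size says "A total of 110 patients will be required for this study", with planned response rates "corresponding to 25% on placebo and 55% on rituximab, assuming a 2-sided 5% significance level". Recruitment says "Participant recruitment is planned over a 36-month period from a maximum of 25 centres across the United Kingdom", and Trial status says "The study is being conducted in 25 sites across the UK". Randomisation names centre as a minimisation factor.

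**The concern.** In a logistic regression fitted by ordinary maximum likelihood, each centre indicator is a nuisance parameter estimated from that centre's few patients. When such parameters grow in number with the sample, the treatment log odds ratio is pushed away from zero and the likelihood ratio statistic no longer follows its reference chi-squared distribution closely. Centres where every patient responds, or none does, contribute nothing.

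The analysis affected is the trial's single confirmatory test and its headline estimate. A false positive would be more likely than the stated 5%. A true benefit would be reported as larger than it is, with an interval that is too narrow and off-centre. The article also intends the data for a later meta-analysis, into which an inflated odds ratio would be carried.

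**Working it through.** **1. The plan's own sample size.** Inputs from Sample size: 25% against 55%, 2-sided 5%, 80% power, so the mean rate is 0.40 and the difference 0.30.

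n = [1.96·√(2·0.40·0.60) + 0.8416·√(0.25·0.75 + 0.55·0.45)]² / 0.30² = (1.358 + 0.555)² / 0.09 = 40.7, so 41 per group.

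With continuity correction: (40.7/4)·[1 + √(1 + 4/(40.7·0.30))]² = 47.1, so 48 per group.

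The plan's 50 per group is close to this. Fisher's exact test at 50 per group has 83.5% power, and 85.3% for "50% placebo and 80% rituximab". With 10% attrition, 100/0.9 = 111.1, against the 110 stated. The sample size reproduces and is not at fault.

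**2. Data per parameter.**
- Patients per centre: 110/25 = 4.4; with 100 evaluable, 4.0.
- Parameters: intercept 1 + centres 24 + treatment 1 + baseline scores 2 + duration 1 + age 1 = 30.
- Expected responders: 55·0.25 + 55·0.55 = 13.75 + 30.25 = 44, or 44/30 = 1.5 per parameter.
- True effect: (0.55/0.45)/(0.25/0.75) = 3.67; log odds ratio 1.299.

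**3. Simulation of the stated analysis** (1,600 to 2,000 trials per scenario). Allocation was 1:1 by minimisation on centre, age and duration with a random element. The logistic model held two baseline scores, duration and age, and treatment was tested by likelihood ratio. Assumptions not in the article: preferred-arm probability 0.8; centre standard deviation 0.3 or 0.5 on the logit scale; equal or skewed expected centre sizes (skewed leaves about 20 of 25 centres recruiting); covariates without prognostic effect; complete data. Null response rates were 25% and 50%.

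| Centres, patients, spread | Type I error: indicators | No centre term | Random intercept | Median OR (true 3.67): indicators | No centre term | Random intercept |
|---|---|---|---|---|---|---|
| 25, 110, equal | 9.4–10.3% | 4.9–5.7% | 6.0% | 6.1–6.2 | 3.7–3.9 | 4.0 |
| 25, 110, skewed | 7.5–8.4% | 4.8–5.9% | 5.7–6.4% | 5.2 | 3.8 | 4.0 |
| 25, 100, equal | 8.6–10.8% | 5.1–5.7% | not run | 6.6 | 3.8 | not run |
| 25, 100, skewed | 7.1–8.6% | 5.3–5.4% | not run | not run | not run | not run |
| 15, 110, skewed | 6.4–8.3% | 5.2–6.4% | not run | 4.7 | 3.9 | not run |
| 10, 110, equal | 7.3–8.0% | 5.6–6.2% | not run | 4.6 | 3.8 | not run |

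The Monte Carlo standard error of the 25-centre indicator-model rates is about 0.6 to 0.8 points; for example √(0.1075·0.8925/1600) = 0.8%. With 25 centres the median log odds ratio is 1.66 to 1.89, that is 1.66/1.299 = 1.27 to 1.89/1.299 = 1.45 times the truth. On average 5 to 10 of the 25 centres had no variation in outcome. Under the null the estimate stayed centred on zero.

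**4. Interval coverage.** Other runs with 25 centres, near-balanced allocation within centre and centre standard deviation 0.3 gave 82% to 86% coverage for the nominal 95% interval under indicator terms. A further check (1,800 trials per scenario, allocation balanced on centre only) gave 83% with equal and 89% with skewed sizes.

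**5. Power.** At 25% against 55% with 110 patients and 25 centres, power was 89% to 90% with indicator terms and 89% to 90% with a random intercept. The remedy gives up nothing.

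**The case against.** The strongest objection is that the article does not fix the harmful model. It never uses the words fixed, dummy or indicator, and a random centre intercept is also a way of including centre. A journal article condenses, and an analysis plan not shown could specify that form, which would largely remove the problem. This stands as a limit: every figure above holds only if centre is fitted as indicator terms. It does not dispose of the point. Centre stands in the same covariate list as age and duration in an ordinary binary logistic regression, and indicator terms are what that wording ordinarily means.

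Four stronger readings are tempting and are not supported:
- A reader might infer indicator terms from the fact that multi-level models are named only under Secondary outcome analyses. Those models are for repeated measures, so the levels may be visits within patients. The contrast settles nothing about centre, and it does not show that a random centre effect is used elsewhere.
- A reader might infer that sparse centres will also break the multiple imputation. The article does not say that centre is in the imputation model, or whether the binary response or the underlying scale score is imputed. Imputation was not simulated.
- A reader might infer that the odds ratio is inflated whatever the truth. The exaggeration needs a true effect.
- A reader might infer that adjusting for centre is itself wrong. Centre is a minimisation factor, so adjustment is reasonable; only the form is in question.

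It is also fair to say that a random intercept does not restore exactly 5%, so the excess due to the form of the centre term is smaller than the whole gap from nominal.

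**Conclusion.** The point holds, conditionally on the plain reading. With centre as unconditional indicator terms and 25 centres, the nominal 5% test runs at roughly 7% to 11%. With 10 to 15 centres it runs at about 6% to 8.5%. If the planned effect is true, an odds ratio of 3.67 is typically reported as about 5 to 6.5 with 25 centres, and the 95% interval covers about 82% to 86% of the time, up to 89% in the most uneven spread checked.

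The direction was the same in every scenario. The size depends on how patients spread over centres, which the article does not give, and on the assumed centre variation, covariate effects and complete data. Because the confirmatory test is affected and the remedy costs almost nothing, the form of the centre term should be settled before unblinding and not left to be inferred.

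**What to change.** Add one sentence to the primary analysis before unblinding: centre enters the logistic model as a random intercept and not as unconditional indicator terms. Conditional logistic regression stratified by centre is an acceptable alternative; it was not simulated here. Pre-specify the fallback for non-convergence: pool centres below a set size, or omit centre. If the analysis plan already says this, only the article's wording needs to be matched to it.

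The cost is small. A random intercept assumes normally distributed centre effects. Its type I error was about 5.6% to 6.5%, close to but slightly above 5%, and its median odds ratio about 4.0 against a true 3.67. The sample size does not change.
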